### Compliance and withdrawal

#### Assessment of compliance

Compliance with study medication (IMP) will be assessed and documented by the research team by checking and recording the number of returned capsules at each visit. This allows any issues to be addressed immediately with the participant. Compliance will be classed as good if between 80 to 100%. The local pharmacy will also document all unused study medication/packaging prior to appropriate reconciliation by the Trial Manager.

### Withdrawal of participants

Participants have the right to withdraw from the study at any time for any reason without giving a reason. The investigator also has the right to withdraw patients from the study drug in the event of inter-current illness, adverse events, serious adverse events, suspected unexpected serious adverse reactions, protocol violations, administrative reasons or other reasons.

Should a participant decide to withdraw from the study, their wishes will be respected. These participants will be asked to complete a “confirmation of withdrawal” form to document their decision. However, for participants that withdraw due to reasons other than related to tolerance of MR scanning, they would be offered the chance to have the primary outcome assessment (cardiac MR imaging) performed at the time of withdrawal.

Participants who have serum TSH <0.4 or >10.0 mU/L on two separate occasions at least 4 weeks apart whilst on study drug will be withdrawn from the study due to safety reasons. For study participants who withdraw from the study, a replacement eligible participant will be recruited, if the study is still recruiting.

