### Administration of the study drug

Participants will be randomised to either LT4 or placebo to be taken orally once daily. This will be discussed at the time of consent and will be clear in the patient information sheet. Initial starting dose of LT4 will always be 25 mcg daily. To achieve the desired target TSH levels in the LT4-treated group (target TSH levels 0.4 to 2.5 mU/L), participants will have their TSH levels checked every 4 weeks and concomitant dose of their LT4 altered by 25 mcg daily, if required. The IMP will be provided as 5 week supplies of LT4 or matching placebo (dispensed separately at each visit), packaged into appropriate individual polypropylene bottles. The label on the bottle will not indicate details of the arm of the study to which the participant has been randomised. The label will instead contain a pack number, which will be the link to the relevant dose.

Study medication will be prescribed by the PI or co-investigator at each site using a trial-specific prescription (documenting the required IMP pack number), and dispensed according to local pharmacy practice. Independent study physicians who will be unblinded will adjust study drug dose as per protocol. The relevant pharmacy will hold a corresponding list allowing the pharmacy staff to correlate the IMP pack number with relevant packaged IMP dose for any particular IMP bottle, thus maintaining the double-blind.

Participants will be informed of potential adverse reactions and advised to contact the relevant study team if required. A study-specific participant contact card will also be provided.

Once randomised, the participant will begin their study medication on Day 0.

At 4, 8, 12 and 24 weeks (+/− 7 days), serum TSH levels will be checked and LT4 doses adjusted as follows (the next bottle of IMP should be started at week 4, 8, 12, 24 +/− 7 days, respectively):

LT4 group:TSH 0.4 to 2.5 mU/L: Continue LT4 at current dose once dailyTSH > 2.5 mU/L: LT4 increased by 25 mcg dailyTSH < 0.4 mU/L: LT4 reduced by 25 mcg, or if already on 25 mcg daily (the lowest possible dose), then recheck TFTs in 4 weeks. If TSH is ≥0.4 mU/L then continue on current dose. Otherwise, if TSH continues to be <0.4 mU/L on the repeat blood test, then the participant will be withdrawn from the study.

Placebo group:Individuals in this group will have a fresh bottle of IMP starting at 4, 8, 12, 24 +/− 7 days after blood tests to maintain the double blind.

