### Statistical analysis

The primary analysis will be an *intention to treat* analysis of change in LVEF before and after levothyroxine therapy. The dependent variable will be LVEF at follow-up; baseline LVEF will be included as a covariate. Residual errors will be assumed to have a normal error distribution. The difference between patients randomised to LT4 and placebo will be fit as a fixed effect. Model assumptions will be checked, and if necessary, transformations of the dependent variable will be considered. A secondary *per protocol* analysis of change in LVEF before and after levothyroxine therapy will also be performed. Both primary and secondary outcomes will be measured at baseline (prior to start of the interventional medication as well as at 52 weeks (end of study). Change in secondary outcomes between the LT4 and placebo groups will be compared using analysis of covariance. Variables that are not normally distributed will be transformed prior to parametric analyses.

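### TSH-triggered withdrawal ends study participation, not only study drug, so the week-52 intention-to-treat analysis can lose outcomes selectively by arm, and replacement does not repair this

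*Protocol article*

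**What the plan says.** Statistical analysis in the protocol article states: "The primary analysis will be an *intention to treat* analysis of change in LVEF before and after levothyroxine therapy". Outcomes are measured at baseline and week 52, and Table 1 schedules cardiac MRI at those two points only.

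Withdrawal of participants says that those with TSH below 0.4 or above 10.0 mU/L "on two separate occasions at least 4 weeks apart whilst on study drug will be withdrawn from the study due to safety reasons". The same section speaks separately of the investigator withdrawing patients from study drug, so the text does know the difference between the two.

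Administration of the study drug makes the triggers arm-specific. For a levothyroxine participant already on the lowest dose, "if TSH continues to be <0.4 mU/L on the repeat blood test, then the participant will be withdrawn from the study". For placebo, a TSH above 10 that persists at a 4-week recheck leads to withdrawal from the study. Pharmacovigilance has a further rule: TSH above 10 with low FT4 is rechecked after 7 days.

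On what follows withdrawal there are two statements. People who leave for reasons other than MR tolerance are told that "they would be offered the chance to have the primary outcome assessment (cardiac MR imaging) performed at the time of withdrawal". And: "For study participants who withdraw from the study, a replacement eligible participant will be recruited, if the study is still recruiting".

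**The concern.** An intention-to-treat comparison at 52 weeks depends on collecting the week-52 outcome from as many randomised participants as possible, whether or not they are still on study drug. Here a conduct rule stops collection, and what sets it off is a laboratory value measured after randomisation that the treatment is meant to change.

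The losses would not be random with respect to arm. Placebo participants enter with TSH of 4.01 to 10.00, so the top of the entry range is their exit threshold. Levothyroxine participants are titrated to 0.4 to 2.5, so the bottom of the target is theirs. Placebo would tend to lose those whose hypothyroidism progresses, and levothyroxine those whose TSH stays suppressed. If either group differs in LVEF recovery from those who remain, the primary difference is distorted. A replacement is a new participant who restores numbers, not the missing outcome.

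**Working it through.** **1. Is a week-52 outcome preserved after a TSH withdrawal?** Four sections bear on it:

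- Withdrawal of participants: out of the study on two out-of-range values at least 4 weeks apart, either arm.
- Administration of the study drug: out of the study on persistent low TSH (levothyroxine, lowest dose) or persistent high TSH (placebo).
- Pharmacovigilance: out of the study if TSH is still above 10 at the recheck.
- Table 1: one follow-up MRI, at week 52, with no line for participants who have stopped.

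None of them retains the participant for the week-52 scan. Scheduled TSH tests fall at weeks 4, 8, 12 and 24. Under the 4-week recheck rules, withdrawal is therefore possible from about week 8 (4 + 4), some 44 weeks before the endpoint.

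**2. Is replacement needed for power?** Inputs from Sample size: difference 3, SD 6 (read as the SD of a single LVEF), two-sided 5%, 90% power, correlation 0.75, 10% drop-out, 47 per arm.

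- Base: 2 × [6 × (1.960 + 1.282) / 3]² = 84.06 per arm.
- Change score, factor 2(1 − 0.75) = 0.50: 42.03, and 42.03 / 0.9 = 46.7, hence 47. This reproduces the stated figure.
- ANCOVA, factor 1 − 0.75² = 0.4375: 36.78, hence 37 evaluable.
- 47 × 0.9 = 42.3, so about 42 are evaluable after the planned loss. Power is then 93.4% with ANCOVA and 90.0% with a change score. ANCOVA keeps 90% until 10 of 47 (21%) are lost.

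The planned number already covers the stated drop-out without replacement.

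**3. How large could the bias be?** The documents give no withdrawal rate and no LVEF for those withdrawn, so these are assumptions. Let w and v be the fractions withdrawn on levothyroxine and placebo, and d₁ and d₂ the mean LVEF of withdrawn minus retained participants in each arm. If the analysis rests on those retained plus replacements who resemble them:

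bias = −(w × d₁) + (v × d₂), where a positive value favours levothyroxine.

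| w | v | d₁ | d₂ | Bias (points) |
|---|---|---|---|---|
| 5% | 5% | −3 | −3 | 0.00 |
| 10% | 10% | −3 | −3 | 0.00 |
| 10% | 5% | −3 | +3 | +0.45 |
| 10% | 0% | −6 | 0 | +0.60 |
| 20% | 5% | −6 | 0 | +1.20 |
| 10% | 10% | 0 | −6 | −0.60 |

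For example, −(0.20 × −6) + (0.05 × 0) = +1.20, and −(0.10 × 0) + (0.10 × −6) = −0.60. Against the 3-point target these extremes are 40% and 20%.

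**4. If a withdrawal scan were used as the follow-up value.** This too is an assumption. Take linear change to the plan's 6 and 3 points over 52 weeks and a scan at week 24, so t = 24/52 = 0.46.

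- w = 20%, v = 5%: levothyroxine 6 × 0.80 + 6 × t × 0.20 = 5.35; placebo 3 × 0.95 + 3 × t × 0.05 = 2.92; difference 2.43.
- w = 0, v = 10%: 6 − (3 × 0.90 + 3 × t × 0.10) = 3.16.

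The estimated difference would be about 2.4 to 3.2 instead of 3.0.

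**The case against.** A reader might infer that the protocol flatly contradicts intention to treat: that withdrawn participants are excluded and replacements analysed in their place. The text does not say so. No sentence removes anyone from the analysis, per protocol is kept as a separate secondary analysis, and replacement only adds randomised participants. The conflict is one of effect, not of literal wording.

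A reader might also take the withdrawal scan as a substitute for the week-52 outcome. Its use is nowhere stated. Such a scan can recover information and is not contrary to intention to treat; how it enters the model belongs in an analysis plan. The offer also sits in the paragraph on people who decide to leave, so it may not reach TSH withdrawals at all.

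Nor is it shown that many participants will be affected. Levothyroxine starts low, Administration of the study drug steps the dose down before withdrawal, and the value must persist on a repeat test. The sample size also accepts 10% drop-out, so an outcome for every participant was never assumed. All of this stands, and it means that material bias cannot be asserted as certain.

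Two things remain. The withdrawal, follow-up and replacement rules are stated here as conduct, and no analysis plan can recover scans that were never taken. And a general drop-out allowance protects power; it does not protect against losses whose cause differs by arm.

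**Conclusion.** The point holds in this form: followed as written, the TSH rules end follow-up on a treatment-driven value with different triggers in the two arms, nothing preserves the week-52 MRI, and replacement does not restore the randomised comparison. The primary LVEF difference may be biased. Size and direction cannot be derived from the document. The illustrated range of roughly −0.6 to +1.2 points rests on assumed rates (5–20% on levothyroxine, 0–10% on placebo) and assumed LVEF gaps of 0 to 6 points; it is about 0 if rates and gaps are alike in both arms. It is not a forecast. It does show that imbalances of this order would be material against a 3-point target, and the loss is avoidable.

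**What to change.** - Leave the TSH thresholds and the clinical rules as the sponsor sets them, but state that meeting them ends study drug and not follow-up.
- Keep the week-52 MRI and the other week-52 assessments for everyone who has not withdrawn consent.
- Analyse every randomised participant in the allocated arm, including any additional recruits.
- Use an MRI taken at withdrawal only as auxiliary or sensitivity data.
- Delete the replacement sentence; the 47 per arm already allows for 10% drop-out.
- Reconcile the TSH rules across Administration of the study drug, Withdrawal of participants and Pharmacovigilance. They differ on the recheck interval (4 weeks or 7 days) and on whether dose reduction comes before withdrawal. These rules decide who leaves; which is right is for the sponsor.

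Cost: protocol and patient-information wording, and the effort of bringing some off-drug participants back for a scan. Table 1 already schedules that scan for every participant; the document gives no budget, so the expense cannot be judged from it.

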### Monitoring, quality control and assurance

The study will be managed by the Chief Investigator, Research Nurse and through NCTU. The Trial Management Group (TMG) will include the Chief Investigator, Trial Statistician, Trial Manager and Research Nurse.

The Principal Investigators will be responsible for conducting the study day-to-day at the site.

The Chief Investigator, Research Nurse and NCTU will provide day-to-day support for the sites and provide training through a site initiation visit and routine monitoring visits.

Quality control will be maintained through adherence to Newcastle Biomedicine Clinical Research Platforms SOPs, study protocol, the principles of GCP, research governance and clinical trial regulations.

An independent Data Monitoring and Ethics Committee (DMEC) comprising independent team members: chair, local expert and statistician will be convened to undertake independent review. The purpose of this committee will be primarily to monitor safety endpoints. The committee will meet at least twice a year after recruitment commences to identify any safety issues.

A Trial Steering Committee (TSC) chaired by an independent lay expert will be established to provide overall supervision of the trial. The TSC will meet at least yearly. At the request of the TSC, interim meetings, in person or by teleconference, will be organised. Any major trial issues may need to be dealt with between meetings, by phone or by email.

Monitoring of study conduct and data collected will be performed by a combination of central review and site monitoring visits to ensure the study is conducted in accordance with GCP and with adherence to the Trial Monitoring Plan, which will be agreed on with the Sponsor. Study site monitoring will be risk-based and will be undertaken by NCTU. The main areas of focus will include consent, serious adverse events, essential documents in study files and drug accountability and management.

Site monitoring plan is likely to include the following:All original consent forms will be reviewed. The presence of a copy in the participant hospital notes will be confirmed for a percentage of participants.All original consent forms will be compared against the study participant identification list.All reported serious adverse events will be verified against treatment notes/medical records.The presence of essential documents in the investigator site file and study files will be checked.Source data verification for a selection of data/participants entered into the study (for example, primary endpoint data and eligibility data).Drug accountability and management will be checked.Central monitoring will include:All applications for study authorisations and submissions of progress/safety reports will be reviewed for accuracy and completeness, prior to submission.All documentation essential for study initiation will be reviewed prior to site authorisation.

All monitoring findings will be reported and followed up in a timely manner.

The study may be subject to inspection and audit by designated staff from the Gateshead Health NHS Foundation Trust under their remit as Sponsor, and other regulatory bodies to ensure adherence to GCP. The investigator(s)/institutions will permit trial-related monitoring, audits, REC review and regulatory inspection(s), providing direct access to source data/documents. The study’s Patient Information Sheets and consent forms will make it clear that this level of access to records is required.

### Pharmacovigilance

The safety of LT4 in this study will be evaluated by examining the occurrences of all adverse events, adverse drug reactions, unexpected adverse reactions, serious adverse reactions or suspected unexpected serious adverse reactions as defined by the Medicines for Human Use (Clinical Trials) Regulations [35]. The relationship and expectedness of the adverse event or reaction (causality) will be assessed by the site investigator and relayed to the chief investigator who, on behalf of the sponsor (Gateshead Health NHS Foundation Trust), will notify the regulatory bodies, the Medicines and the Healthcare Products Regulatory Agency (MHRA) and the research ethics committee (REC), within 7 days for fatal and life-threatening events and 15 days for non-life-threatening events. All study investigators will be notified.

Most adverse events and adverse drug reactions that occur in this study, whether they are serious or not, will be expected treatment-related toxicities due to the drugs used in this study. For a full list of expected undesirable effects of Levothyroxine, please refer to the relevant Summaries of Product Characteristics [29,30].

We do not anticipate adverse effects of LT4. Nevertheless, safety of participants is of paramount importance, and therefore, LT4 dose will be commenced at a small dose (25 mcg daily) and the dose increased every 4 weeks by 25 mcg daily until the serum TSH is within the required range. Safety measures (ECG, symptoms of heart failure, and pulse oximetry) will be assessed at visits 2 to 6. If severe hypothyroidism develops (TSH >10 mU/L with low FT4 levels), then symptoms including fatigue, weight gain and poor memory may develop. For such individuals, we will recheck TFT in 7 days. If serum TSH remains above 10 mU/L, then such patients will be withdrawn from the study. In addition, we will assess the health of participants via a health status questionnaire. Participants will also be provided with a helpline number in case they experience any problems.

For purposes of this protocol:All non-serious adverse events will be recorded at the follow-up visits 2 to 6.Any serious adverse events will be recorded throughout the duration of the trial until week 52 (+/− 3 days).Serious adverse events exclude any pre-planned hospitalisations (for example, elective surgery) not associated with clinical deterioration.Serious adverse events exclude routine treatment or monitoring of the studied indication (that is, hypothyroidism), not associated with any deterioration in condition.Serious adverse events exclude elective or scheduled treatment for pre-existing conditions that did not worsen during the study.

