LT4 treatment based on the above regimen will continue for a total of approximately 52 weeks at which point the final set of study specific assessments will be made (with a further follow-up phone call at approximately 53 weeks). If a participant in the placebo arm has a TSH >10 mU/L then their TFTs will be rechecked in 4 weeks. If, the TSH is ≤10 mU/L on the repeat test then the participant will continue with the study and, if, the TSH continues to be >10 mU/L then the participant will be withdrawn from the study. At the final visit, participants on each arm of the study will stop their IMP and will be referred back to their GP to have their thyroid function checked in 6 to 12 weeks. The GP and the patient will be encouraged to discuss whether there is a need to commence LT4 therapy in these individuals based on the clinical situation. The GP letter (sent once the participant is randomised) and the GP follow-up letter (sent after each participant completes their IMP) outlines the suggestion to recheck TSH levels at 6to 12 weeks for each participant once they have completed their IMP.

At the end of each visit, participants will be asked to return any surplus study drug in the original packaging to the study team, who will verify and document compliance. All unused study medication and packaging will be sent to the local pharmacy for documentation and destruction as per local policy (following appropriate reconciliation by the Trial Manager). Documentation of prescribing, dispensing and return of study medication shall be maintained for study records.

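### The TSH rules for keeping or withdrawing a participant conflict, chiefly between the dose-adjustment rule and the general withdrawal rule, and no precedence is stated

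*Protocol article*

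**What the plan says.** All references are to the protocol article.

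- **Administration of the study drug, LT4 arm, low TSH.** The response to a TSH below 0.4 is "LT4 reduced by 25 mcg, or if already on 25 mcg daily (the lowest possible dose), then recheck TFTs in 4 weeks". Withdrawal follows that recheck: "if TSH continues to be <0.4 mU/L on the repeat blood test, then the participant will be withdrawn from the study". In context this applies only to someone already on the lowest dose.
- **Administration of the study drug, LT4 arm, high TSH.** Any TSH above 2.5 leads to a 25 mcg increase. No upper TSH limit is given, and there is no withdrawal step.
- **Administration of the study drug, placebo arm.** "If a participant in the placebo arm has a TSH >10 mU/L then their TFTs will be rechecked in 4 weeks". Someone whose second value is 10 or lower stays in; someone still above 10 is withdrawn. FT4 is not mentioned.
- **Withdrawal of participants.** "Participants who have serum TSH <0.4 or >10.0 mU/L on two separate occasions at least 4 weeks apart whilst on study drug will be withdrawn", for safety reasons. The rule does not depend on arm, dose or FT4, and the two values need not be consecutive.
- **Pharmacovigilance.** "If severe hypothyroidism develops (TSH >10 mU/L with low FT4 levels"), the instruction is "For such individuals, we will recheck TFT in 7 days", with withdrawal if TSH is still above 10. No arm is named.

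None of these sections refers to another or says which prevails.

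**The concern.** Some TSH histories lead to continuation under one section and removal under another. The general rule is described as a safety rule, so it should give one answer.

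There is also a statistical consequence. The primary analysis is by intention to treat on LVEF at 52 weeks (Statistical analysis). Whoever is withdrawn from the study may have no scan at that time. Two low TSH values would be expected mainly on levothyroxine. Two values above 10 are handled by dose increase in one arm and by recheck and withdrawal in the other. The choice of section could therefore change the number of missing 52-week scans, and change it unequally between arms.

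**Working it through.** The plan gives no figure to reproduce. The check is to find which histories are feasible and read each rule literally against them.

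**Feasible doses.** The start is always 25 mcg, with 25 mcg steps at the week 4, 8, 12 and 24 checks. The highest dose a participant can be taking when tested is:

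- week 4: 25 mcg
- week 8: 25 + 25 = 50 mcg
- week 12: 25 + 2 × 25 = 75 mcg

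The first test above 25 mcg is thus at week 8, and a second low value can come at week 12. Week 12 is the earliest point of conflict for low TSH. For TSH above 10 it is week 8.

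**Spacing.** Visits carry a window of ±7 days. Visits nominally 28 days apart can fall 28 − 14 = 14 to 28 + 14 = 42 days apart. Weeks 12 and 24 (84 days) fall 70 to 98 days apart, so the 4-week gap is always met there.

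**Histories (illustrative values).**

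| History | Administration of the study drug | Withdrawal of participants | Pharmacovigilance |
|---|---|---|---|
| A. LT4: below 0.4 at week 12 on 75 mcg and at week 24 on 50 mcg | Reduced again, kept | Withdrawn | Not triggered |
| B. LT4: below 0.4 at week 8 on 50 mcg and at week 12 on 25 mcg, at least 28 days apart | Kept, recheck in 4 weeks | Withdrawn at week 12 | Not triggered |
| C. LT4: 10.8 at week 4, 10.4 at week 8, normal FT4, at least 28 days apart | Increased, kept | Withdrawn | Not triggered |
| D. Placebo: 11 with low FT4, 10.5 at 7 days, 9 at 4 weeks | Kept | Condition not met | Withdrawn at day 7 |
| E. LT4: same values as D | Kept | Condition not met | Withdrawn at day 7 |
| F. Placebo: 10.5, 9, 10.5 at 4-week intervals, normal FT4 | Kept, new recheck due | Withdrawn | Not triggered |
| G. Placebo: 10.5, 10.6 four weeks apart, normal FT4 | Withdrawn | Withdrawn | Not triggered |
| H. LT4: below 0.4 twice on 25 mcg, 4 weeks apart | Withdrawn | Withdrawn | Not triggered |

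A and C are the main conflicts. C is plausible because entry TSH may be as high as 10.00 (Inclusion criteria) and titration starts at the lowest dose. B differs only by one further recheck. D and E depend on whether the 7-day rule is a special case. F turns on whether the two values must be consecutive. In G and H the rules agree.

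**The case against.** **The dosing text is not a withdrawal rule.** On this view, one reduces the dose after the first low value and withdraws after the second, and both sections are obeyed. That is a possible reading, but the dosing text contains its own withdrawal step and ties it to the 25 mcg dose. The general rule drops that condition, which changes who leaves.

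**The 7-day recheck is a special rule for a more severe state.** A reader might infer a flat contradiction because 7 days cannot satisfy a 4-week gap. The documents do not support that inference. The general rule gives a condition that suffices for withdrawal and does not say it is the only one; the same section lets the investigator stop study drug for adverse events or other reasons. What stands is that the placebo rule makes no FT4 exception and no precedence is stated.

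**Every section contradicts every other.** They do not. The LT4 and placebo instructions cover different arms, and G and H show agreement. A placebo participant with TSH below 0.4 is covered only by the general rule, which is a gap and not a conflict.

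**Sites will act differently.** The documents do not show this. Independent unblinded physicians adjust the dose and the site team is blinded. The ambiguity remains for whoever applies the rules.

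**The outcome is not lost.** The withdrawal section offers cardiac MR at withdrawal, and replacement while recruitment is open. Both help in part. A scan at week 12 is 52 − 12 = 40 weeks before the planned one. A replacement does not restore the 52-week value of the randomised participant who left.

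**Conclusion.** The point holds as a conflict in stated text; it is not a detail that a condensed article leaves to the full protocol. It is firm for the LT4 arm, with TSH below 0.4 above 25 mcg or TSH above 10 on two tests at least 4 weeks apart. It is secondary for TSH above 10 with low FT4, and for non-consecutive values above 10 on placebo.

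The effect on missing 52-week LVEF cannot be sized, because the documents give no rate of repeated out-of-range TSH. A reader might infer that the general rule would consume the drop-out allowance, since 10% of 47 per arm is 4.7 participants. That would follow only if about 10% of the LT4 arm had two low values, and nothing in the documents supports that rate. No effect on the primary result is shown. The case for correction is that a safety withdrawal rule that helps decide who stays to the primary endpoint has more than one reading.

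The conclusion assumes that each section is read literally and that tests fall on the listed visits, with the 28-day gap met where stated.

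**What to change.** Reconcile the LT4 and placebo instructions in Administration of the study drug with Withdrawal of participants and Pharmacovigilance, giving one rule for each trigger:

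1. TSH below 0.4
2. TSH above 10
3. TSH above 10 with low FT4

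For each, state the arm or arms, the dose level at which it applies, the recheck interval, whether the values must be consecutive, and which rule takes precedence when two apply. State also how the 4-week gap is judged given the ±7-day visit window. Put the rules in one place and cross-refer to them elsewhere. The clinical team decides the content of each rule; no view is taken here.

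The cost is protocol wording only. Sample size, visit schedule and analysis model are unaffected.
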